### Screening and eligibility

Orthopaedic surgeons-in-training in their first, second or third specialist training year in the West Midlands Workforce Deanery will be eligible to participate in the trial. Eligible trainees will be identified by liaison with the training programme directors for Trauma & Orthopaedic surgery in the three West Midlands schools; Warwick, Birmingham and Oswestry. An invitation email will be sent to all eligible trainees by programme administrators at the deanery.

#### Inclusion criteria

Trauma & Orthopaedic surgeon-in-training in West Midlands school (Warwick/Birmingham/Oswestry).In specialty training years 1–3.Willing and able to attend a 2-day cadaveric simulation training course at the West Midlands Surgical Training Centre (WMSTC), Coventry.

#### Exclusion criteria

Unavailable on course dates.

### Consent

#### Surgeon participants

Potential study participants will be provided with written and verbal information about the study. Consent will be obtained by the trial team. The right to refuse participation without giving reasons will be fully respected, and enrolled participants will be free to withdraw from the study at any time without reason, and without prejudice to their training. All participants will be provided with the contact information of a team member who can provide further information about the study. All participants who are allocated to the control group will have the opportunity to undertake the cadaveric simulation training intervention at the end of the study follow-up. This provision is being offered so that the control group are not disadvantaged in their access to educational opportunity by virtue of being randomised to the control group.

#### Patients whose operations are assessed

Patients who undergo an operation by a surgeon who is participating in the study will not be separately consented to allow access to radiographs to assess their implant position or clinical outcome data. Permission to access this information for the purposes of this study without patient consent has been granted from the confidentiality advisory group (16/CAG/0125). It is recognised that seeking consent from a group of primarily elderly, frail patients to assess low risk, routine clinical data in a secure manner for a trial they are not directly participating in would be unduly burdensome for the patients. All patient data will be fully anonymised and handled securely in line with university data regulations.

### Randomisation

Participants will be randomised at the point of recruitment using block randomisation (block size 4) to generate a random sequence list, to which participants will be assigned in the order that they enter the study. The allocation sequence will be generated by a senior medical statistician, participants will be enrolled by the trial team.

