#### The cadaveric simulation training course

The course will be delivered in September at the start of the surgical training year (which runs August to August). The course will take place in the WMSTC at the University Hospital Coventry & Warwickshire (UHCW). The WMSTC is a specialised wet-laboratory facility for delivering cadaveric training, and has an experienced dedicated faculty to facilitate training delivery.

The course will consist of two full days of teaching, with expert consultant faculty teaching on fresh-frozen hemi-cadavers (waist-to-toe-tip). The participant:faculty ratio will be 2:1, and participant:cadaver ratio will be 2:1. Each participant will undertake each of the four procedures in their entirety as primary surgeon (‘skin-to-skin’), and will act as assistant when their partner is the primary surgeon four times. Hence each participant is exposed to eight procedures during the course.

The environment and psychological fidelity of the simulation will be maximised by providing:

Full surgical dress including masks, gloves, gowns and lead X-ray aprons.The usual disposable surgical drapes.Skin preparation (iodine solution) to prepare the surgical site, and participants and faculty will be asked to observe the usual sterile field precautions as in real theatre.Full surgical instrument trays, surgical implants and cement (for hemiarthroplasty) of the same type as in real theatre will be used.Image intensifier (mobile X-ray) will be available for intraoperative use.Background noise levels and room temperature were maintained at what would usually be expected in the operating theatre.

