### Blinding

The participants cannot be blinded to the type of training they receive, neither can the trial team in organising the cadaveric simulation training. The trial team will take no part in the training of participants. The assessment of radiographic images will be made blinded to group allocation.

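### One-at-a-time allocation in fixed blocks of 4, with an unblinded trial team enrolling and no stratification by training year, makes allocations partly predictable and leaves experience to chance

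*Protocol article*

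**What the plan says.** All references are to the protocol article.

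- **Method.** The Randomisation section says: "Participants will be randomised at the point of recruitment using block randomisation (block size 4) to generate a random sequence list". The list is one "to which participants will be assigned in the order that they enter the study". No stratification factor is named.
- **Roles.** The same section separates two tasks: "The allocation sequence will be generated by a senior medical statistician, participants will be enrolled by the trial team". Under Consent (Surgeon participants): "Consent will be obtained by the trial team".
- **Blinding.** "The participants cannot be blinded to the type of training they receive, neither can the trial team in organising the cadaveric simulation training". For outcome assessment: "The assessment of radiographic images will be made blinded to group allocation".
- **Size and timing.** The Sample size section caps each arm at 16, the capacity of the training centre for the single course that could be funded. On timing: "The course will be delivered in September at the start of the surgical training year". The exclusion criterion is being unavailable on the course dates.
- **Experience.** Trainees in specialty years 1 to 3 are eligible. The Clinical outcomes section treats procedure time as falling with experience. The Statistical analysis plan section compares months of training and prior procedures between arms at baseline and adjusts the linear mixed models for surgeon experience. Complications and health state receive descriptive between-group comparisons.

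**The concern.** With a constant 2:2 block, whoever knows the block size and has seen the allocations so far can count what is left in the current block. Keeping the list itself hidden does not prevent this. Here the people who take consent and enter trainees also organise the course, and for that task they are not blinded. They are therefore well placed to know who has been allocated to it.

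At stake is whether the order or timing at which a particular trainee enters could depend on the arm that comes next. With at most 32 surgeons, each contributing repeated operations, one steered enrolment moves a whole cluster of observations. Blinded reading of radiographs guards against biased measurement, not against arms that differ in aptitude or motivation from the start. Covariate adjustment cannot repair selection on traits that are not measured.

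A second, smaller issue is training year. The plan regards surgeon experience as an important covariate, yet three training years share one list, so their balance across arms is left to chance in a small sample.

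**Working it through.** **Inputs from the protocol article.** Two arms; block size 4; maximum 16 per arm (16 places, one course), so 32 in total. An allocation of 2:2 within each block is inferred from the equal arms. Check: 32 / 4 = 8 blocks, and 8 × 2 = 16 per arm, which agrees with the stated maximum. There is no power calculation to reproduce.

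**Predictability, given knowledge of the block size and earlier allocations.** The six orderings of AABB are equally likely.

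| Position in block | Probability that it is certain | Probability that a best guess is right |
|---|---|---|
| 1 | 0 | 1/2 |
| 2 | 0 | 2/3 |
| 3 | 1/3 (first two alike) | 1/3 × 1 + 2/3 × 1/2 = 2/3 |
| 4 | 1 | 1 |
| Sum per block | 1.333 | 2.833 |

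- Certain: 1.333 / 4 = 33.3%; over 8 blocks 8 × 1.333 = 10.7 of 32 (minimum 8, maximum 16).
- Best guess right: 2.833 / 4 = 70.8%; over 8 blocks 22.7 of 32. An unpredictable sequence would give 50%.

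**Effect of varying the block size.** With sizes 4 and 6 chosen at random, and staff knowing the pair of sizes but not which one is in use, simulation gives about 6% of allocations certain and a best guess right about 69% of the time. Certainty nearly disappears, but guessing hardly changes.

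**Balance of training year.** The article gives no mix of years, so 11/11/10 in years 1/2/3 is an assumption, split 16:16 at random.

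- Mean year = (11 + 22 + 30) / 32 = 63/32 = 1.97. Sum of squares about the mean = 145 − 63²/32 = 20.97; variance = 20.97 / 31 = 0.676.
- SD of the between-arm difference in mean year = √(0.676 × (1/16 + 1/16)) = 0.29.
- With a, b and c trainees of years 1, 2 and 3 in one arm (a + b + c = 16), each split has probability C(11,a) C(11,b) C(10,c) / C(32,16). Summing over splits whose means differ by at least 0.5 year gives 8.3%. The same sum for assumed mixes of 16/8/8 or 8/8/16 gives 14%.
- Year-3 split of 7:3 or worse: 2 × Σ C(10,c) C(22,16−c) / C(32,16) for c = 7 to 10 = 2 × (0.0993 + 0.0239 + 0.0028 + 0.0001) = 25%.

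**After stratified batch allocation, same assumed mix.** With 16 per arm, the best achievable split is 6/5/5 against 5/6/5. The means are 31/16 and 32/16, a difference of 0.06 year.

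**The case against.** The strongest reply is that predictability is conditional. The block size is printed in this article, but nothing says that enrolling staff knew it during recruitment. Nor does the article say who held allocations or how they were released. The trial runs in a registered clinical trials unit under its operating procedures, and concealment may be described in the full protocol. That stands: the article's silence on concealment is not counted against it, and the figures above carry the condition.

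A reader might also infer that the trial team controls the sequence. It does not, because a statistician generates it. That separation is sound, but it does not stop prediction from past allocations.

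The route to bias is also narrow. The pool is closed and objectively defined, programme administrators email every eligible trainee, and controls are offered the course after follow-up. What remains is influence over when a given trainee's consent is taken and entered.

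On training year, chance imbalance under randomisation is not bias. The mixed models adjust for surgeon experience, so it would be wrong to infer that an imbalance would simply appear as a training effect. The adjustment does help for implant position, procedure time and radiation dose. It rests on at most 32 surgeons, however, and does not reach the descriptive comparisons of complications and EQ-5D. Stratification is therefore useful rather than essential.

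**Conclusion.** The point holds in conditional form. The stated choices (one fixed block size, entry-order assignment, enrolment by an unblinded team) leave about a third of allocations certain and a 71% guessing rate for anyone who knows the block size and earlier allocations. These percentages measure predictability, not bias. The documents do not support the stronger readings that a third of allocations were in fact known in advance, or that every comparison is biased.

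The training-year part is modest. The chance of a difference of half a year or more is about 8% under the assumed 11/11/10 mix and 14% under the two more uneven mixes, all before adjustment. The chance of a year-3 split of 7:3 or worse is about 25% under the first mix.

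The exposure is avoidable. With one course on fixed dates, and availability for those dates required for entry, the cohort can be known before anyone is allocated. Allocating at the point of recruitment has no evident advantage.

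**What to change.** Replace allocation at recruitment with a single step. Complete consent and enrolment first. Then have the same statistician allocate the whole cohort in one batch before the September course, stratified by training year and with at most 16 per arm. Include training year in the mixed models. No trainee then enters after any allocation is known, so foreknowledge is removed whatever the enrolling staff know.

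The cost is one rewritten paragraph and a new list, with no extra participants or staff. The small downside is that trainees learn their allocation slightly later.

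If sequential allocation has to stay, randomly varying block sizes that are not disclosed to enrolling staff are only a weak fallback. Sizes 4 and 6 cut certain allocations from 33% to about 6% but leave best-guess success near 69%. In that case the protocol should also state who knows the block sizes and the earlier allocations during recruitment.

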### Postrandomisation withdrawals

Withdrawn participants will not be replaced.

### Study setting

The study participants will be on training rotations within the regional hospitals of the West Midlands during the study follow-up. The hospitals where trainees have been working, and performing operations, during the study follow-up will be identified from the participants electronic surgical logbook records.

### Interventions

#### Control group

The control group will undertake standard residency training according to the master-apprentice model, which is the current standard practice in UK. No additional training or access to learning materials will be provided beyond the fortnightly didactic teaching sessions which are delivered as a part of routine training.

#### Intervention group (cadaveric simulation trained)

Participants allocated to the intervention group will receive an intensive, 2-day cadaveric simulation training course at the start of the training year, where four common orthopaedic surgical procedures will be taught (DHS, hemiarthroplasty, ankle fracture fixation and lower limb fasciotomy). All intervention participants will receive training on all four procedures, which will be considered separately in the analysis as individual substudies (as they have different radiographic outcome measures). The fasciotomy procedure is included as a ‘filler’ to make the course structure work, and chosen because it is an important high-stakes, anatomically critical operation that is rarely performed by trainees. Outcomes related to the fasciotomy procedure will not be collected or included in the analysis.

#### The cadaveric simulation training course

The course will be delivered in September at the start of the surgical training year (which runs August to August). The course will take place in the WMSTC at the University Hospital Coventry & Warwickshire (UHCW). The WMSTC is a specialised wet-laboratory facility for delivering cadaveric training, and has an experienced dedicated faculty to facilitate training delivery.

The course will consist of two full days of teaching, with expert consultant faculty teaching on fresh-frozen hemi-cadavers (waist-to-toe-tip). The participant:faculty ratio will be 2:1, and participant:cadaver ratio will be 2:1. Each participant will undertake each of the four procedures in their entirety as primary surgeon (‘skin-to-skin’), and will act as assistant when their partner is the primary surgeon four times. Hence each participant is exposed to eight procedures during the course.

The environment and psychological fidelity of the simulation will be maximised by providing:

Full surgical dress including masks, gloves, gowns and lead X-ray aprons.The usual disposable surgical drapes.Skin preparation (iodine solution) to prepare the surgical site, and participants and faculty will be asked to observe the usual sterile field precautions as in real theatre.Full surgical instrument trays, surgical implants and cement (for hemiarthroplasty) of the same type as in real theatre will be used.Image intensifier (mobile X-ray) will be available for intraoperative use.Background noise levels and room temperature were maintained at what would usually be expected in the operating theatre.

The simulated operating theatres will be set up within the WMSTC as two parallel round-robin circuits. The two stations requiring X-ray use (DHS and ankle open reduction internal fixation (ORIF)) will be set up at the far end of the room to create a radiation zone and where appropriate, standard precautions will be used. Careful consideration will be given to the optimum sequential use of the cadaveric specimens in planning the course structure. For example, it is necessary that the DHS station precedes the hemiarthroplasty station as it would obviously not be possible to perform a DHS operation when the femoral head had been removed. Similarly, the fasciotomy incisions would compromise the soft tissue envelope of the lower limb to a sufficient degree that the fidelity of the ankle ORIF station would be compromised. It is important to make the best and most efficient use of the cadaveric material, for both ethical and financial reasons.

### Blinding

The participants cannot be blinded to the type of training they receive, neither can the trial team in organising the cadaveric simulation training. The trial team will take no part in the training of participants. The assessment of radiographic images will be made blinded to group allocation.

### Adverse event management

In the unlikely event of a serious adverse event, the chief investigator will report to the sponsor (University of Warwick), ethics committee and project supervisors.

### Patient and public involvement

There was no direct patient or public involvement in the design of the study, although clearly training competent surgeons is in the public interest. There is qualitative work to be done around this trial to better understand patient expectations of surgical training.

### End of trial

The trial will end when all the radiographic and clinical outcome data have been collected from the participating sites. The trial will be stopped prematurely if required by the ethics committee, following recommendations from the sponsor, or if funding for the study is withdrawn. The research ethics committee and confidentiality advisory group will be notified in writing once the trial is complete.

### Trial oversight

This trial is being undertaken as part of a doctoral research project ([name]), and supervised by three senior supervisors (DG, [name], [name]). The supervisors will act as the trial management group and steering committee. The trial is being conducted within a registered Clinical Trials Unit (CTU), and will follow the CTU SOPs.

### Data collection plan

Data on the numbers of procedures performed by the participating surgeons at baseline will be collected. The operations performed by the participants during study follow-up will be identified by the surgeons’ electronic logbook. Only procedures coded as ‘S-TS: supervised-trainer scrubbed’ or ‘S-TU: supervised trainer unscrubbed’ will be included in the analysis. This is to ensure that only procedures where the trainee has performed the key parts (S-TS) or the entire procedure (S-TU) are included. If further information on supervisor input/takeover is required this can be obtained by accessing the corresponding procedure based assessment (PBA) record for the operation. PBAs are routinely collected as part of training.

Procedure data will be extracted and anonymised to study identifier by the electronic logbook data team, before being sent to the trial team. The data will include operation type, date, hospital, hospital ID, patient age, American Society of Anaesthesiologists Grade and supervision code. The radiographs and clinical outcome data relating to these procedures will then be obtained from the study sites via liaison with the respective Research & Development Departments. Data will be entered into a secure trial database on a professionally encrypted trial-specific computer, fully anonymised with only study identifiers. Once data collection is complete, and prior to analysis, range checks for data values will be undertaken, and data will be double checked on entry to the statistical software package. The project supervisors will act as the data monitoring committee. No interim analysis will be undertaken. The trial team and statistician will have access to the final trial dataset.

### Statistical analysis plan

Baseline data including completed months of training and number of prior procedures performed will be summarised and compared between the two arms of the study. A CONSORT chart showing the flow of participants through the study will be produced. The three taught procedures (substudies 1–3) will be analysed and reported individually.

The main analysis will investigate and report differences between the two groups with respect to the implant positions (as measured from radiographs), the procedure times, the intraoperative radiation dose to the patient, and patient outcomes, as measured by postoperative complications and health state at 4 months postoperation (hip fractures only).

Statistical tests will be two-sided and considered to demonstrate a significant difference when p<0.05. Temporal trends by group for implant position, procedure time and radiation dose will be presented. Linear mixed-effects models will be fitted to allow for within-surgeon correlation between repeated observations (surgeon clustering as a random effect), and to adjust for important covariates such as patient condition, age and surgeon experience. These will be summarised by plotting individual learning curves, and then modelled to estimate the overall learning curves for the two arms of the study.

Descriptive statistical analyses of between-group comparisons will be presented for complication rate and health state, with temporal analysis of the latter being reported if appropriate and feasible. The statistical analysis will be supervised and checked by a senior medical statistician at Warwick University.

In the event of missing data, statistician advice will be sought on multiple imputation.

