## Aim

The aim is to determine which of the two surgical training strategies for junior orthopaedic surgeons-in-training lead to the best patient outcomes for three common procedures.

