#### Substudy 1: DHS

Primary outcomeTip–apex distance (mm).Secondary outcomes (in order of importance)Lag screw position in the femoral head (defined by Cleveland Zones).Plate flush to lateral femoral cortex (binary Y/N).Eight cortex hold for plate screws (binary Y/N).

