#### Substudy 3: ankle fracture fixation

Primary outcomeMedial clear space (mm).Secondary outcomesLateral malleolar displacement (mm).Tibiofibular clear space (mm).Talocrural angle (degrees).Medial malleolar displacement (mm).

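### The p<0.05 rule lets every tested outcome demonstrate a difference, although each substudy has one named primary outcome

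*Protocol article*

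**What the plan says.** The protocol article sets up a hierarchy of outcomes and then states a decision rule that makes no use of it.

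- **Hierarchy.** Under Radiographic outcomes, each substudy has one primary: tip–apex distance (substudy 1), leg length discrepancy (substudy 2) and medial clear space (substudy 3). For substudy 1 the other radiographic measures appear under "Secondary outcomes (in order of importance", and substudy 2 is laid out the same way. Substudy 3 lists its secondaries with no ranking: "Secondary outcomesLateral malleolar displacement (mm" and three more.
- **Decision rule.** The Statistical analysis plan section says that two-sided tests will be "considered to demonstrate a significant difference when p<0.05". The sentence before it puts the outcome domains together: "The main analysis will investigate and report differences between the two groups with respect to the implant positions (as measured from radiographs), the procedure times". That sentence continues with radiation dose, complications and EQ-5D. The words primary and secondary do not occur in this section.
- **Separate reporting.** "The three taught procedures (substudies 1–3) will be analysed and reported individually".
- **Descriptive outcomes.** The same section plans descriptive between-group analyses for complications and health state.
- **Status of the work.** The Abstract calls it exploratory, and the Sample size section replaces a power calculation with a capacity limit of 16 surgeons per arm.

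**The concern.** The rule says what a p-value below 0.05 will be taken to show, and it says so for every test. On its terms, a difference in stem alignment, talocrural angle or fluoroscopy time is demonstrated in the same sense as a difference in the named primary. The Abstract does not help: it describes the primary outcome as technical success judged by implant position on the radiograph, which would fit any of the 13 radiographic measures (4 + 4 + 5).

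The trial has at most 32 surgeons and no power calculation. A single nominal p-value among several outcomes is therefore weak evidence, yet the plan would let it be reported as a demonstrated effect. The Introduction says that evidence is needed before large investment in cadaveric training, and the results are to go to Health Education England. A chance finding on a minor measure could be cited for or against that investment.

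**Working it through.** **Inputs from the protocol article**

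| Substudy | Radiographic measures | Procedure time | Radiation measures | Tests k |
|---|---|---|---|---|
| 1 DHS | 1 primary + 3 = 4 | 1 | 2 | 7 |
| 2 Hemiarthroplasty | 1 primary + 3 = 4 | 1 | 0 | 5 |
| 3 Ankle | 1 primary + 4 = 5 | 1 | 2 | 8 |

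The radiographic counts come from the three substudy sections. Procedure time and the two radiation measures (fluoroscopy time and dose) come from Clinical outcomes, which excludes radiation for substudy 2. Complications and EQ-5D are left out as descriptive. The total is 7 + 5 + 8 = 20. The article does not state that each listed measure gets its own test, so the count is a reading of the lists. If radiation is one measure, the counts are 6, 5 and 7, total 18.

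**Step 1: the plan's own figure.** With k tests at level 0.05, no effect on any outcome and independent tests, the chance of at least one p<0.05 is 1 − 0.95^k. For k = 1 this is 5.0%, the stated per-test level. That is the error rate of each named primary taken alone.

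**Step 2: all tested outcomes in a substudy, independent.**

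- Substudy 2, k = 5: 1 − 0.95^5 = 22.6%
- Substudy 1, k = 7: 1 − 0.95^7 = 30.2%
- Substudy 3, k = 8: 1 − 0.95^8 = 33.7%

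With radiation counted once, substudy 1 (k = 6) gives 26.5% and substudy 3 (k = 7) gives 30.2%. Substudy 2 is unchanged.

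**Step 3: correlated outcomes.** The article gives no correlation between outcomes. They come from the same operations and surgeons, so independence is unlikely. The test statistics were simulated as normal with a common correlation ρ (400,000 draws, two-sided 5% each):

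| Assumed ρ | k = 5 | k = 7 | k = 8 |
|---|---|---|---|
| 0 | 22.6% | 30.1% | 33.7% |
| 0.2 | 21.9% | 28.6% | 31.9% |
| 0.3 | 20.9% | 27.2% | 30.0% |
| 0.5 | 18.3% | 22.9% | 24.9% |
| 0.7 | 14.9% | 17.9% | 19.1% |
| 0.9 | 10.1% | 11.5% | 11.8% |

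Even at ρ = 0.9 the chance is about twice the per-test level.

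**Step 4: after restricting the claim to the primary.** One test per substudy carries the claim, so the rate within a substudy is 5.0%. The chance that at least one of the three primaries falls below 0.05, if independent, is 1 − 0.95^3 = 14.3%.

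**The case against.** The strongest reply is that nothing confirmatory is at risk. Each substudy has one pre-named primary tested at 5%, the substudies are reported separately, and the work is called exploratory. Unadjusted secondary outcomes are a recognised choice in such work, and an article may leave their interpretation to a fuller analysis plan. The article never claims a 5% familywise rate, so there is no stated figure to correct. The count of tests is inferred, and independence is implausible.

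Most of this stands, and it limits the point. The primary claims are not inflated, and 23% to 34% is an upper range under independence. What does not stand is that the matter is merely left open. The section states what p<0.05 will demonstrate, without restriction, directly after a sentence that puts all outcome domains into one main analysis. An exploratory label is a reason for softer wording on secondary outcomes, and this wording is confirmatory.

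A reader might go further in two ways that the documents do not support.

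- **That a false claim somewhere in the trial is more likely than not.** Pooling all 20 tests gives 1 − 0.95^20 = 64.2% under independence. With an assumed correlation of 0.5 within and 0.3 between substudies, simulation gives 48.9%, and a common 0.5 gives 42.1%. The plan also does not pool the substudies.
- **That the three primaries must be adjusted against each other.** The Aim asks "which of the two surgical training strategies for junior orthopaedic surgeons-in-training lead to the best patient outcomes for three common procedures", which could invite an overall statement, but the analysis section plans no pooled claim.

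**Conclusion.** The point holds as a defect in the stated decision rule. The rule allows a demonstrated difference on any tested outcome and so sets aside the single primary per substudy that the article itself names. If training has no effect, the chance of at least one such difference within a substudy is up to 23% (substudy 2) to 34% (substudy 3) under independence, and about 18% to 25% at an assumed correlation of 0.5. These figures rest on one test per listed measure, no effect on any of them, and a correlation that the article does not give. Learning-curve or temporal-trend tests, if made, would add to the count. The error rate for each named primary remains 5%.

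**What to change.** In the Statistical analysis plan section, replace the general rule with wording such as:

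*For each substudy, a two-sided p<0.05 on its primary outcome (tip–apex distance for DHS, leg length discrepancy for hemiarthroplasty, medial clear space for ankle fixation) will be taken to demonstrate a difference between the arms. All other outcomes will be reported as estimates with 95% confidence intervals; any p-values for them are nominal and supportive.*

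Naming the three measures here also settles the broad description of the primary outcome in the Abstract.

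**Cost.** The change is two sentences, and the primaries lose no power. The real loss is that secondary results, including procedure time, can no longer be presented as demonstrated differences, however small their p-values.

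**Optional.** The team could instead test the secondaries in a fixed order, but the article ranks radiographic secondaries only for substudies 1 and 2 and gives procedure time and radiation no place in that ranking. Such a sequence would also bar all secondaries from a claim once the primary missed p<0.05. A Holm adjustment over the three primaries would be needed only if the team wished to make one claim across substudies. Neither is required while the substudies are reported individually.
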